**Methods and analysis:**

The QM2-RC encompasses three interconnected projects (Project 1, 2, and 3) aimed at developing a quality management strategy and evaluating its impact on system performance across New York State. This report specifically focuses on Project 3, which involves a stepped-wedge trial with 35 clinics receiving a quality management intervention that includes performance coaching. This intervention will be compared to a treatment-as-usual (TAU) condition for clinics not participating in the trial. Administrative data will be utilized to monitor outcomes over four years. The coaching intervention, guided by the Integrated Promoting Action on Research Implementation in Health Services (i-PARIHS) model, emphasizes interpreting quality measures and applying insights to enhance care. Coaches will provide support on data utilization, patient-centered care, harm reduction strategies, and the use of patient monitoring tools. The trial aims to evaluate clinic staff and leadership attitudes, experiences, and behaviors through surveys, semi-structured interviews, and external facilitator notes. Primary clinic outcomes will be assessed through adverse events, decreased clinic rates of substance use related emergency department visits and hospitalizations as well as mortality among patients within the first 12 months after admission to treatment after adjusting for individual and community level characteristics. This study is being developed over a multi-year period and will be informed by a mixed-methods approach incorporating multiple data sources, qualitative interviews, patient and clinic surveys. The study is being conducted in partnership with New York State Office of Addiction Services and Supports (OASAS) and will be informed by input from patient, providers, health insurers, family members and local governing units.

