We will initiate a stepped wedge randomized controlled trial involving 1) 35 clinics receiving a performance coaching intervention and 2) a treatment as usual (TAU) condition for all clinics not participating in the intervention. Additionally, qualitative interviews with stakeholders and surveys of all 550 outpatient clinics will be conducted at three different points in time (years 1, 3, and 4). We will use administrative data from 2021–2027, including records from the Office of Addiction Services and Supports (OASAS) treatment registry, Medicaid, and vital statistics, to monitor client outcomes. This concurrent mixed-methods study [94] will evaluate the impact of the OASAS QM2 strategy on patient outcomes and statewide stakeholders, focusing on retention in care and adverse events (emergency department visits, hospitalizations, and mortality). Clinics will be randomized to one of five sequences, varying the timing of the intervention between years 2 and 4.

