## Materials and methods

### Project 3 aims: Conduct a stepped-wedge trial that includes two conditions: 1) 35 clinics receiving a performance coaching intervention and 2) a treatment as usual (TAU) condition for all clinics not participating in the intervention to examine the effect of the OTP intervention on THD, retention in care, and adverse events

The SPIRIT checklist was used as a guide for reporting this study protocol (Fig 1). To assess the impact of the OASAS QM2 strategy on care retention and adverse events using a stepped-wedge, mixed-methods design across SUD treatment clinics. Clinics will be recruited to participate in this stepped wedge trial by State partners via email invitations, announcements via State listservs, and announcements at relevant meetings to contact the Project Manager or the Principal Investigators. A total of 35 clinics will be recruited after October 2025. The aim of the intervention is to help clinical staff interpret their quality measures and implement subsequent quality improvement efforts through facilitators. The intervention will be six months long for each clinic and be informed by the i-PARIHS model [95].

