### Data and analytic plans

#### Project 3: Stepped-wedge trial.

*Quantitative Methods:* We will utilize Generalized Linear Mixed Models (GLMMs), which are commonly applied in the analysis of stepped-wedge trial [106,107]. The models will be structured as follows:

$$F(\mu_{ijk})=\mu +\beta_{j}+{\delta X}_{ij}+\alpha_{i}+\phi_{ik},\;\alpha_{i}\sim N\left(\text{0},\tau_{\alpha }^{\text{2}}\right),\;\gamma_{ij}\sim N(\text{0},\tau_{\phi }^{\text{2}})$$

where $\beta_{j}$ represents a fixed effect for time, $X_{ij}$ is an indicator for intervention in clinic *i* at time *j* (coded 0 for the control condition, then 1 from the start of the intervention in the clinic until the end of the study), and δ denotes the intervention effect. The models include random effects to account for clustering at both the clinic and individual patient levels, which are assumed to follow a normal distribution with mean zero and variances $\tau_{\alpha }^{\text{2}}$ and $\tau_{\phi }^{\text{2}}$, respectively. We will estimate the intervention effect while controlling for secular trends and adjusting for clustering within clinics ($\alpha_{i}$) and individual ($\phi_{ik}$), using mixed effects modeling with a binary distribution and logit link function. The models will be fitted using the *glmmTMB* package in R software [108,109]. The primary outcome will be adverse events, and the fixed-effects coefficients for the intervention effect, exponentiated, will indicate the extent to which the intervention changes the rate of adverse events. An offset term can be included to capture client differences in time at risk due to timing of treatment entry.

TAU clinics will be included in the model with an indicator variable. A post-hoc test of the intervention effect coefficient will compare TAU and performance coaching, and a TAU-by-time interaction will assess time trends within the TAU group. The GLMM analysis will be expanded by adding the clinics not receiving the performance coaching intervention during the study period. For TAU clinics, the intervention indicator will be coded 0 in all periods. This provides an additional estimate of trends ($\beta_{j}$) in outcomes in a much larger sample of clinics. Because the fixed effect for time ($\beta_{j}$) is estimated, the intervention effect (δ) can be interpreted as the degree to which performance coaching results in a lower rate of adverse events than what would be expected due to time alone in the absence of intervention.

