If we observe significant treatment effects (e.g., reduced adverse events) from the performance coaching intervention, we will conduct follow-up analyses to strengthen causal inference. Drawing on methods from treatment mechanism research, we will test whether hypothesized mediators (e.g., person-centered care, retention in treatment) are associated with outcomes. We will also examine moderation by population characteristics and regional variation (e.g., gender, location), as well as provider-level differences in implementation. Lagged treatment effects will be assessed using interaction terms between treatment and time since intervention start by cohort. These exploratory analyses will inform interpretation and guide qualitative inquiry.

*Data and specification:*

We will join multiple administrative data sources from New York State for years 2021–2027 to form our analytical dataset. We will use Client Data System (CDS), Medicaid claims, and NYS vital statistics data to form the analytic dataset. The OASAS treatment registry (CDS) will provide extensive clinical data on clients at treatment admission and will include descriptions of providers through the provider data system (PDS). Medicaid will provide medical diagnoses, healthcare services, SUD treatment services, and medication utilization data. The New York State Vital Statistics will be received from the outpatient clinics in the form of all-cause mortality for clients participating in the trial. Additional OASAS data will provide operational and staffing information for each clinic. To date, 75% of clients in the OASAS registry have been linked to Medicaid claims data.

Quality measures from Project 1 will encompass patient, clinic, and organizational factors, including demographics, clinical complexity, substance use patterns, prior healthcare utilization, community access, substance use trends, resources, psychosocial interventions, clinic structure, staffing, and MOUD use and retention. Primary outcomes include adverse events, healthcare utilization, and mortality. Adverse events are defined as SUD-related hospitalizations or emergency department visits, including overdose, within 12 months of treatment entry. Healthcare utilization includes all-cause emergency department visits or hospitalizations within the same timeframe. Mortality will be assessed as all-cause mortality. Outcome variables will be risk-adjusted to account for client health status.

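### The article names one primary outcome in its model and power text but three in its data specification, and defines adverse events both with and without death

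*Protocol article*

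**What the plan says.** **Number of primary outcomes**

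- Quantitative Methods (under Project 3: Stepped-wedge trial): "The primary outcome will be adverse events". The power paragraph's heading also uses the singular, and its main and subgroup figures both start from the 0.23 adverse-event rate.
- Data and specification, same section: "Primary outcomes include adverse events, healthcare utilization, and mortality".
- Abstract, Methods and analysis: "Primary clinic outcomes will be assessed through adverse events, decreased clinic rates of substance use related emergency department visits and hospitalizations as well as mortality". This is also plural. It includes mortality but not all-cause utilization, so it is a different set again.

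**Content of adverse events**

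- Introduction, last paragraph: "adverse events (emergency department visits, hospitalizations, and mortality". Death is inside, and the visits and admissions are not restricted by cause.
- Data and specification: "Adverse events are defined as SUD-related hospitalizations or emergency department visits, including overdose, within 12 months of treatment entry". Death is not named, and all-cause mortality is listed as its own outcome. On utilization the same paragraph says: "Healthcare utilization includes all-cause emergency department visits or hospitalizations within the same timeframe".

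Alpha = 0.05 appears once, in the power paragraph, for adverse events.

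**The concern.** The primary outcome and its definition decide what the trial may claim. With two counts of primary outcomes in one section, a reader cannot tell whether a significant effect on all-cause utilization or mortality, without one on adverse events, would be a positive trial. The follow-up analyses of mediators and moderators open on a significant treatment effect, with reduced adverse events given only as an example, so that gate is open to the same doubt.

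The second conflict touches the one outcome that was powered. An endpoint of any-cause ED visit, admission or death is broader than one of ED visits and admissions related to substance use disorder, and will normally have a different event rate. The 0.23 baseline can belong to only one of them.

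**Working it through.** **1. The stated power figure, with adverse events as the single primary outcome.** Inputs from the power paragraph: 35 clinics, 5 crossover points with 7 clinics each, 350 clients per clinic per period, ICC 0.05, alpha 0.05 (two-sided assumed), baseline 0.23, RR 0.93.

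- Observations: 35 × 350 × 6 periods (baseline plus 5 steps) = 73,500, as stated.
- Target rate: 0.23 × 0.93 = 0.2139, which rounds to the stated 0.21.
- Detectable RR at 80% power under a Hussey–Hughes model (fixed period effects, one random clinic intercept): 0.932 to 0.935 with binary variance and 0.923 to 0.926 with Poisson variance. These bracket the stated 0.93. At exactly 0.93, power is 82.7% to 85.4% (binary) or 72.1% to 75.8% (Poisson), so the match is on the rounded detectable RR.

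The figure is therefore consistent with one primary outcome tested at 0.05.

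**2. If the three outcomes were all primary and any one sufficed.** Assumption, not stated in the article: each is tested at two-sided 0.05.

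- Upper bound: 3 × 0.05 = 0.15.
- Independent tests: 1 − 0.95³ = 0.143.
- Equally correlated tests, by simulation:

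| Correlation | Family-wise error |
|---|---|
| 0 | 14.3% |
| 0.5 | 12.5% |
| 0.7 | 10.9% |
| 0.9 | 8.4% |

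Under the Data and specification definitions, adverse events are a subset of all-cause utilization, so at least that pair of tests should be positively correlated. The independence figure is probably too high.

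**3. If the three outcomes shared 0.05 by Bonferroni.** Each is tested at 0.05/3 = 0.0167, with critical value 2.394. A design with exactly 80% power at 0.05 has a standardized effect of 1.960 + 0.842 = 2.802. Power becomes Φ(2.802 − 2.394) = Φ(0.408) = 65.8%. Restoring 80% needs ((2.394 + 0.842)/2.802)² = 1.33 times the information.

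**4. If all three had to succeed.** Alpha is not inflated, but joint power cannot exceed that of the weakest test. The article gives no mortality rate. Assuming 0.5% to 3% per period and ICC 0.001 to 0.05, power for mortality at RR 0.93 is about 6% to 18%.

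**5. The two definitions side by side.**

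| | Introduction | Data and specification |
|---|---|---|
| ED visits, hospitalizations | cause not limited | related to substance use disorder, overdose included |
| Death | included | not named; all-cause mortality listed separately |

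The power paragraph gives 0.23 without saying which column it belongs to. It also expresses the rate per 6 months, while the Data and specification definition uses 12 months from treatment entry, so the window needs confirming too.

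**The case against.** The strongest reply is that the passages that matter most for inference already agree: the model text and the power text both take adverse events as the single primary outcome, and the stated power is consistent with that. The plural sentence could then be loose wording. This lowers the cost of repair, but it does not remove the conflict, because the plural sentence stands in the paragraph that defines the outcomes.

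A reader might infer several stronger points that the article does not support:

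- **That 0.05 is spent three times.** No sentence says that utilization or mortality is tested at 0.05. A multiplicity rule may sit in an analysis plan that is not shown, so its absence here is no finding. The 8% to 14% is conditional.
- **That power for the other outcomes was never worked out.** The power paragraph speaks of specific outcomes in the plural, and an article may print only the main result.
- **That a fatal overdose counts as a good outcome.** The Data and specification definition includes overdose, says nothing on a death without hospital contact, and records mortality separately. The optional offset concerns timing of treatment entry and does not settle the matter, but detailed handling of death commonly belongs in the analysis plan.
- **That retention is a lost outcome.** The Introduction describes the evaluation as "focusing on retention in care and adverse events (emergency department visits, hospitalizations, and mortality", and Data and analytic plans names retention as a possible mediator. The aims heading, "to examine the effect of the OTP intervention on THD, retention in care, and adverse events", contains an undefined abbreviation and a label that does not match performance coaching. That is an editorial slip and adds no weight here.

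**Conclusion.** The concern holds as two contradictions within the article: one primary outcome against several, and adverse events with death and any-cause contacts against adverse events restricted to contacts related to substance use disorder. Neither depends on an unseen document, and an analysis plan that added a multiplicity rule would leave both published statements in conflict.

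The consequence depends on the reading. With adverse events as sole primary outcome, alpha stays at 0.05 and the stated 80% stands, provided that 0.23 belongs to the definition used. With three primary outcomes each at 0.05 and any one sufficing, family-wise error would be about 8% to 14% for correlations from 0.9 down to 0 (bound 15%). With a Bonferroni split, power for adverse events would fall from 80% to about 66%. These last figures rest on assumptions about testing that the article does not state. The power check further assumes a two-sided test and a single random clinic effect that is constant over time.

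**What to change.** 1. Keep adverse events as the sole primary outcome at alpha 0.05, as Quantitative Methods and the power paragraph already have it.
2. Write one definition and use it in the Abstract, the Introduction, Quantitative Methods and Data and specification. It should say whether visits and admissions are limited to substance use disorder and whether death counts as an event.
3. State that the 0.23 baseline and RR 0.93 refer to that definition and its time window, or recompute them.
4. Reword Data and specification so that all-cause utilization and all-cause mortality are secondary, tested in a fixed order or with Holm's procedure.

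Merely ending time at risk at death would not settle item 2: it has no direct place in the stated binary logit model, and it would leave a fatal event uncounted.

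Cost: mortality and utilization lose primary status. If death is not added and 0.23 already matches the definition chosen, the change is one of wording. If death is added, the baseline rate and the power figure must be rechecked. The choice should be made before outcome data are examined; Ethics approval gives October 1, 2025 as the start of access to retrospective data.

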Before the trial begins, clinics receiving the QM2 intervention will be randomized into six cohorts of six-month long interventions over three years. Clinics are randomized to onset of intervention in one of six time periods over the three years of the intervention rollout (years 2–4 of the project) and tracked using administrative data. Administrative data will be used for all clinic clients during each of the seven six-month periods (n ≈ 350/clinic) will be drawn from administrative data. The first six-month period will be a baseline prior to any intervention. Six clinics will be assigned randomly to one of six time periods for onset of intervention. Using administrative data, we will track clients within each clinic over four years, including a pre-intervention six-month baseline period. During the same four-year period, clients in clinics not participating in the stepped-wedge trial will be tracked to better understand changes in outcomes under treatment as usual (TAU) and to compare the outcomes of those clinics with clinics receiving the quality management intervention. We anticipate a final study population of approximately 91,000 individuals per year who are receiving treatment from one of the 571 enrolled outpatient substance use treatment programs. Because this is a stepped-wedge trial, all clinics (and as a result all clients within the clinics) will eventually get the intervention, the randomization will have to do with when the clinic is randomized rather than being assigned to a control or intervention group. Fig 2 illustrates the structure of the stepped-wedge trial.

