*Statistical Analyses of the Proposed Stepped-Wedge Trial:* Analyses will begin with examination variable distributions, appropriate transformations, and patterns for, followed by formal imputation methods if needed [110–112]. We will use Generalized Linear Mixed Models (GLMM) for the stepped-wedge design [106].

*Power Analysis for Primary Outcome Statistical power:* Power estimation for specific outcomes was conducted using PASS 2022 software and Monte Carlo simulation [113]. Sample size and baseline rates (μ) were estimated using administrative data. For 80% power, α = 0.05, ICC = 0.05, and a 5-crossover-point stepped-wedge-RCT with 7 clinics starting at each point, power calculations indicate 80% power to detect a small decrease (RR = 0.93) in adverse events with 35 clinics and 350 clients per clinic per 6-month period (n ≈ 73,500 total observations). This corresponds to a decrease from 0.23 to 0.21 events per 6 months. In racial/ethnic subgroups (10% of clients, n ≈ 35 per site), power remains 80% to detect a modest decrease (OR=0.78), from 0.23 to 0.18.

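### The primary outcome covers 12 months from admission, but exposure and power are set per six-month period; the unit of analysis and the handling of windows that span a crossover need to be fixed together

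*Protocol article*

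**What the plan says.** **Outcome.** The Data and specification part of the stepped-wedge analysis section states: "Adverse events are defined as SUD-related hospitalizations or emergency department visits, including overdose, within 12 months of treatment entry". The abstract's Methods and analysis paragraph gives the same horizon, "within the first 12 months after admission to treatment". The Quantitative Methods paragraph names adverse events as the primary outcome.

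**Exposure.** The intervention indicator is indexed by clinic and time and is "coded 0 for the control condition, then 1 from the start of the intervention in the clinic until the end of the study". Coaching itself is shorter: "The intervention will be six months long for each clinic". No transition period is described.

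**Data.** The design text in Materials and methods (after Fig 1) says "Administrative data will be used for all clinic clients during each of the seven six-month periods", with about 350 per clinic.

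**Model.** The intervention effect is estimated "using mixed effects modeling with a binary distribution and logit link function", with random effects for clinic and individual. On follow-up time: "An offset term can be included to capture client differences in time at risk due to timing of treatment entry".

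**Power.** The power paragraph uses 35 clinics, five crossover points with seven clinics each, 350 clients per clinic per six months, ICC 0.05 and RR 0.93, and adds: "This corresponds to a decrease from 0.23 to 0.21 events per 6 months".

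**The concern.** The outcome window is twice the length of a step, so a client's 12 months touch two or three periods, and for many clients the clinic changes status part-way through. The coefficient δ has a clear meaning only if the plan says which events, in which rows, are set against which exposure status. The article gives the outcome, the exposure coding, the model and the power basis, and they do not combine into one analysis.

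Two things are at stake. One way of joining the pieces puts a large amount of post-crossover time into control rows near the crossover, where a stepped wedge draws much of its information. The other way avoids that, but leaves the sample size behind the 80% power without a basis. A choice between them made after results are seen would be data-dependent.

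**Working it through.** **1. Reproducing the plan's figure.** Observations: 35 × 350 × 6 = 73,500, as stated.

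Power was checked with the standard stepped-wedge generalised least squares (GLS) variance: clinic random intercept, fixed period effects, five sequences of seven clinics, six periods, two-sided α = 0.05 (sidedness is not stated).
- Total variance: 0.23 × 0.77 = 0.1771
- Between-clinic variance: 0.05 × 0.1771 = 0.0089
- Variance of a clinic-period mean within clinic: 0.95 × 0.1771 / 350 = 0.00048
- SE(δ): about 0.0054
- Difference: 0.23 − 0.93 × 0.23 = 0.0161
- Power: Φ(0.0161/0.0054 − 1.96) = Φ(1.02), about 85%

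Across binomial variants power is 83–85%, with a detectable RR of 0.932–0.935. With Poisson variance it is 72–76%, with a detectable RR of 0.923–0.926. The stated RR of 0.93 at 80% power is therefore matched to its two decimals. The inputs are a six-month rate and client-period counts.

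**2. Reading A: one 12-month outcome per client, coded by the clinic's status in the admission period.** A client admitted u months before crossover has (12 − u)/12 of the window after it.
- Last period before crossover: u averages 3, so the share is 9/12 = 75%.
- One period earlier: u averages 9, so the share is 3/12 = 25%.
- Control clinic-periods: 7 × (1+2+3+4+5) = 105. Of these, 7 × 5 = 35 are at 75% and 7 × 4 = 28 at 25%. So 63/105 = 60% are affected.
- Mean share over all control cells: (35 × 0.75 + 28 × 0.25)/105 = 32%.

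The expected estimate comes from putting these shares, with 1 in all exposed cells, in place of the outcome in the same GLS estimator while X stays coded 0/1. This assumes uniform admissions and an effect proportional to the exposed share.

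| Setting | Expected estimate / true effect |
|---|---|
| 35 clinics, 5 × 7 | 0.27 |
| 6 × 6 layout | 0.34 |
| 5 × 7, all admitted at period start | 0.57 |
| 5 × 7, all admitted at period end | about 0 |
| 5 × 7 plus about 500 TAU clinics (assumed number, shared time effects) | about 0.61 |

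At 0.27, a true RR of 0.93 would show as 1 − 0.07 × 0.27 = 0.98. At 0.61 it would show as 1 − 0.07 × 0.61 = 0.96.

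With the six-month inputs, power in the 35 clinics falls from about 85% to about 13%. Those inputs do not belong to a 12-month outcome. With an assumed 12-month risk of 1 − 0.77² = 0.41 against about 0.38, and 100 to 350 admissions per clinic-period, it is about 9–23%. With about 500 TAU clinics and the six-month inputs it is about 79%, but the estimate is still only 61% of the true effect.

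**3. Reading B: client-period rows, exposure taken for the period of the event.** The 12-month window then causes no dilution. But the outcome exists only within 12 months of entry, whereas 350 counts all clinic clients. The share within 12 months is not given. Same formula, 35 clinics alone, RR 0.93:

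| Clients per clinic-period within 12 months (assumed) | SE(δ) | Power |
|---|---|---|
| 350 | 0.0054 | about 85% |
| 250 | 0.0064 | about 70% |
| 175 | 0.0076 | about 55% |
| 100 | 0.0100 | about 35% |

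**The case against.** The strongest reply is that the article never assigns a 12-month outcome to the admission period. Its text leans towards client-period rows: data on all clients in each period, an individual random effect that would have little purpose with one binary outcome per client, an offset for timing of entry, and a count of 73,500 client-periods. The 12 months may simply limit which events count, and 0.23 per six months may be the same event expressed per period. This stands, and it means dilution is not established.

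It is also fair that the TAU clinics are to be added to the model, which lessens the loss under reading A; that the ratio within the 35 clinics depends strongly on admission timing; and that an effect at full strength from the first day of coaching is assumed, not stated. The TAU result itself needs shared time effects and would not carry over to a fully free TAU-by-time interaction.

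Finally, a condensed article may leave row structure to a fuller document. The absence of a detailed coding rule is therefore not the point here. The point is that the outcome, period and power statements that are printed disagree.

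Two features of the plan might seem to repair this but do not. The offset is optional and concerns time at risk, not exposure status. The lagged-effect analysis is exploratory and is run only after a significant effect.

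**Conclusion.** The conflict holds: a 12-month outcome from admission, exposure by six-month period, and power on a six-month rate in all clinic clients. On neither reading does the stated 80% power belong to the outcome as defined.

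A reader might infer that the trial's effect estimate will be diluted to about a quarter and reported as null. The article does not support that. It follows only under admission-period coding, which is nowhere stated. Even then the figure is 27% (5 × 7) or 34% (6 × 6) under uniform admissions, about 0 to 57% in the 5 × 7 layout by admission timing, and about 61% with some 500 TAU clinics sharing the time effects.

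Under event-period coding the dilution from the window is nil, and what remains is an unsupported n. Power for the 35 clinics alone is about 70%, 55% or 35% at the assumed 250, 175 or 100 eligible clients.

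The difference between the five-step layout in the power paragraph and the six cohorts and seven periods in the design text is a separate matter. It is used here only to show both layouts.

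**What to change.** Make the primary analysis unit the client by six-month calendar period. Count SUD-related emergency department visits or hospitalisations in person-time within 12 months of admission, take the exposure indicator for the period in which the event falls, and carry time at risk in the model as a set part of it instead of an option. Report the 12-month-from-admission outcome as secondary, excluding admissions whose window straddles the clinic's crossover; in the 5 × 7 layout this keeps 105 − 63 = 42 control clinic-periods. Restate n per clinic-period and power for clients within 12 months of entry, using the administrative data already drawn on for the baseline rate. Settle this before outcome data are analysed.

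The cost is protocol wording and a different cut of the same administrative data. The downside is fewer clients per clinic-period, because longer-stay clients leave the primary analysis, and a less favourable stated power for the 35 clinics.
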